### Hypotheses

We hypothesize that youth receiving the FCFN intervention will have increased rates of mental health treatment initiation and engagement compared with youth receiving standard of care. We will also explore hypothesized mechanisms of intervention impact (eg, navigator satisfaction, youth treatment motivation, and perceived barriers to care) as well as potential moderators (eg, sex, race, ethnicity, and out-of-home placement status).

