### Intervention Condition (FCFN)

Families (n=40) who are randomized to the FCFN intervention will complete six 60-minute intervention sessions in the first 2 to 3 months of the 6-month period. Sessions can be scheduled on a weekly or biweekly basis. The 6 sessions, described in Figure 2, are as follows: *Introduction to the navigator and navigation services*, *Specialty mental health services orientation*, *Clinical care team mapping*, *Barriers to care and stress management*, *Therapy expectations and stigma*, and *Values and motivation to engage in treatment*. The 6-month intervention period also includes brief check-ins with youth and caregivers, typically conducted through the Fostering Connections web application, by telephone and videoconferencing, depending on the preference and availability of families. The 6 intervention sessions will be audio recorded to separately assess for FCFN intervention fidelity by trained study staff (raters).

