##### Cascade Outcomes

GLMM analyses of dichotomous outcomes (screening, treatment initiation, etc) will include intervention (FCFN group vs control group) as a fixed between-participants effect. Cox regression analysis (PROC PHREG) will be used to compare the interventions on time-to-event outcomes (eg, time to assessment) using a shared frailty model that accounts for clustering within pods. The potential mediators and mechanisms of change, measured longitudinally (at baseline and at 1, 3, and 6 months) only for FCFN intervention participants, will be initially examined for intervention impact using GLMMs that include a repeated within-participants time effect. The majority of the mediators are scaled variables, anticipated to have normal distributions, but final models and link functions will be chosen based on observed distributions. It will not be possible to test mediation without data from the control group. Therefore, we will identify potential mediators to be studied in the future trial by first determining which potential mediators change between baseline and month 1 or month 3 and then examining whether month 1 or month 3 values and changes between baseline and month 1 or month 3 are associated with cascade outcomes.

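### The second screening step for candidate mediators names no baseline term, so a scale whose mean shifts can be listed because its pre-intervention level is prognostic

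*Protocol article*

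**What the plan says.** The Hypotheses section of the protocol article sets out the exploratory aim: "We will also explore hypothesized mechanisms of intervention impact (eg, navigator satisfaction, youth treatment motivation, and perceived barriers to care"). The procedure is in Statistical Analysis, under Cascade Outcomes. The scales are introduced as "The potential mediators and mechanisms of change, measured longitudinally (at baseline and at 1, 3, and 6 months"), and they are analysed "only for FCFN intervention participants, will be initially examined for intervention impact using GLMMs that include a repeated within-participants time effect". The arm is planned at 40 families (Intervention Condition).

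The article concedes the limit of this analysis: "It will not be possible to test mediation without data from the control group". It therefore sets a two-step screen to find candidates for a later trial:

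- Step 1: "first determining which potential mediators change between baseline and month 1 or month 3".
- Step 2: "examining whether month 1 or month 3 values and changes between baseline and month 1 or month 3 are associated with cascade outcomes".

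The article gives no significance level for either step. It does not say whether a scale must succeed on the value, on the change, or on both, and it names no covariates for step 2.

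**The concern.** The screen is meant to find scales whose movement after baseline goes with better service outcomes. The matching null hypothesis is that, given where a youth started, the later value is unrelated to outcome. Neither predictor named in step 2 tests that null on its own.

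- **Follow-up value.** It carries the baseline level with it. Youth who arrive motivated tend to stay motivated and may also start treatment more often. The test can then reject although change plays no part.
- **Change score.** It is negatively correlated with baseline. If baseline is prognostic, change is associated with outcome in the opposite direction, again without any effect of its own.

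Step 1 looks only at the average shift. It does not show whether the youth who changed more are those with better outcomes. At stake is the list of potential mediators carried forward: a prognostic level could be listed as a candidate, and a real candidate could show a null or reversed change association.

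**Working it through.** The protocol states no power, alpha or error rate for this screen, so there is no figure to reproduce.

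**Inputs from the article.** FCFN arm only, n=40; dichotomous cascade outcomes; step 1, then step 2, as quoted.

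**Assumed inputs (none is in the article).** Outcome prevalence about 50%; baseline odds ratio 2 or 3 per SD; stability s (correlation of baseline with follow-up) 0.5 or 0.7; mean shift 0 or 0.5 SD; two-sided 0.05; step 1 read as a paired t test; one visit and one outcome.

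**Algebra.** Let m0 be the baseline value and m1 the follow-up value, both with variance 1.

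1. Cov(m0, m1 − m0) = s − 1 and Var(m1 − m0) = 2(1 − s), so the correlation of change with baseline is −√((1 − s)/2). This is −0.50 at s = 0.5 and −0.39 at s = 0.7.
2. If the linear predictor is a·m0 + b·m1, its covariance with change is a(s − 1) + b(1 − s) = (b − a)(1 − s). A real effect b > 0 gives no change-score association when a = b, and a reversed one when a > b.
3. With baseline in the model, γ·m0 + β·m1 = β(m1 − m0) + (γ + β)·m0. Value and change then share the coefficient β, so they are one test.

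**Simulation.** m1 = shift + s·m0 + √(1 − s²)·e and logit P(y) = log(OR)·m0, so change has no effect of its own. There were 4,000 trials per cell, with logistic regression and Wald tests. "Either" means value or change significant.

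| OR | s | Shift (SD) | Step 1 passed | Value | Change | Either | Step 1 and either | Value given baseline |
|---|---|---|---|---|---|---|---|---|
| 2 | 0.5 | 0 | 5.2% | 12.6% | 13.2% | 25.5% | 1.5% | 3.8% |
| 2 | 0.5 | 0.5 | 87.6% | 14.0% | 13.0% | 26.4% | 23.2% | 4.7% |
| 2 | 0.7 | 0 | 5.2% | 24.3% | 9.9% | 33.5% | 1.8% | 4.4% |
| 2 | 0.7 | 0.5 | 97.8% | 24.0% | 10.2% | 33.3% | 32.6% | 3.7% |
| 3 | 0.5 | 0 | 5.0% | 24.0% | 24.3% | 46.8% | 2.6% | 4.1% |
| 3 | 0.5 | 0.5 | 86.2% | 23.8% | 24.9% | 47.0% | 40.6% | 3.9% |
| 3 | 0.7 | 0 | 4.6% | 45.4% | 15.1% | 57.6% | 2.8% | 3.8% |
| 3 | 0.7 | 0.5 | 98.0% | 46.0% | 15.8% | 58.6% | 57.3% | 4.2% |

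The Wald test is somewhat conservative at this size. With likelihood-ratio tests and the same inputs, the value alone rejects in 17% to 54% and the change alone in 11% to 31%. Step 1 plus either test gives about 31% to 66% with the mean shift and about 1.5% to 3.7% without it. The value given baseline rejects in about 5% to 6%.

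**Three checks on the reading.**

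- *Two tests alone do not explain the excess.* With odds ratio 1 and a 0.5 SD shift, step 1 plus either test selects 5.8% to 7.4% (Wald, s = 0.5 and 0.7).
- *Step 1 works only through the mean.* The joint rate is close to the product of the two steps: at OR 3, s = 0.7, shift 0.5 it is 0.980 × 0.586 = 0.574, against 0.573 simulated. Once the mean moves, step 1 gives almost no protection.
- *Entering value and change together does not help if each coefficient is read separately.* Baseline is then implicit (value minus change), but the coefficients pick up its effect and are significant in 27% to 79% of trials (s from 0.3 to 0.7).

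**The case against.** **The article is silent on covariates, and those of an exploratory model are often left to the full protocol or SAP.** This stands in part. Baseline is not named, but it is not excluded either, and a reader who infers that the plan rules out baseline adjustment goes beyond the text. Still, the article does choose its predictors. Listing value and change as separate things to examine adds nothing once baseline is in the model, because they are then the same test. The wording therefore reads most naturally as unadjusted.

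**Step 1 already removes stable traits.** This stands for a scale whose mean does not move: about 1.5% to 3.7% are selected. A reader might infer that any stable prognostic trait will enter the list, and the procedure does not support that. The problem is confined to scales whose mean also shifts. Those are plausible cases, since the FCFN sessions address barriers to care and motivation for treatment, and both are named as possible mechanisms. Step 1 is also single-arm, so a natural time trend can pass it.

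**The article does not say that either test suffices.** This stands. The 31% to 66% belongs to an assumed either-test rule. Requiring both tests to be significant gives about 1% to 7%, because a baseline-only predictor pushes the two coefficients in opposite directions. A careful analyst who looks at both might notice this.

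**Adjustment is not a complete cure.** This stands. If a stable trait drives outcome and is measured with error at both visits, the adjusted test still rejects in 11% to 25% (correlation 0.5 to 0.7, odds ratio 2 to 3 per SD of the true trait). Some measures also have no baseline to adjust for. Randomization follows the baseline assessment, so nobody has a navigator to be satisfied with at that point.

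**Nothing is declared a mechanism.** This stands and limits the severity.

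**Conclusion.** The point holds in a limited form and is minor. As worded, step 2 does not separate a prognostic starting level from change after baseline. A scale that passes step 1 can therefore be listed as a candidate although individual change is unrelated to outcome. The size depends on the assumed odds ratio, stability, prevalence, mean shift and selection rule, none of which the article gives. It is large only when the mean shifts and either test suffices.

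A reader might infer that the trial will report false mechanisms or an invalid mediation test. The documents do not support this: mediation testing is expressly disclaimed, the output is a list for a later trial, and no between-arm result is touched. The change is worth making because the list is the only product of this step and the baseline value of the relevant scales is already collected.

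**What to change.** In Statistical Analysis, Cascade Outcomes, reword step 2 as follows.

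- For scales with a meaningful pre-intervention value, such as treatment motivation and perceived barriers, relate the month 1 (or month 3) value to the cascade outcome in a model that also contains the baseline value of the same scale. Base candidate selection on the follow-up coefficient. It is the same test as change, so one test replaces two and no either-or-both rule is needed.
- Report unadjusted associations, if at all, as prognostic only.
- For measures with no pre-intervention value, such as navigator satisfaction, keep the follow-up value and label the association descriptive.
- Note that adjustment reduces the bias but does not fully remove it when baseline is measured with error.

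The cost is a few sentences and one extra parameter in models of about 40 youth. At 50% prevalence that is 40 × 0.5 = 20 events for two predictors, or 10 per predictor. No new data are needed.

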Despite high need for evidence-based mental health services for CWI youth, ample evidence suggests that coordination between child welfare and mental health service systems is inadequate. Access to care for CWI youth is hampered by multiple system-level barriers, such as frequent change of placement as well as underreporting of mental health problems by foster parents, social workers, and physicians [13]. National survey data (n=3803) highlight a substantial gap between the identified need for and use of mental health services in child welfare populations, particularly among older youth: 66% of those aged 11 to 14 years have clinically significant mental health needs, yet only 26% use mental health services [21]. Data local to the site of the proposed project demonstrate critical gaps in mental health screening and full assessment, with only 28% of all youth assessed within 2 months of case opening, 45% by 3 months, and 69% by 6 months. Furthermore, by 12 months, 11% of youth had their case closed before ever receiving a mental health assessment [22].

The public health impact of gaps in mental health services delivery among CWI youth is significant. Untreated mental health concerns among CWI youth persist when they leave the out-of-home care system and transition to independence [23]. CWI youth are also likely to have dual (or *crossover*) involvement with the juvenile legal system [24], which can further exacerbate unmet services needs and disparities within this population. Persistent mental health concerns in this population can also contribute to placement instability [25] and re-entry into the child welfare and juvenile legal systems [26], which both compound mental health difficulties and strain public health systems and economies. Unaddressed mental health services needs also perpetuate racial and ethnic disparities in services access, engagement, and quality in this population, as well as perpetuate the root causes of these disparities (eg, systemic racism and discrimination), which have notable public health consequences. Data local to the site of the proposed project mirror national statistics, documenting the alarming overrepresentation of African American and Latinx youth in the child welfare system [21]: 36% of CWI youth aged 12 to 17 years are African American compared with 6.1% of the entire county population.

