### Assessment Data Collection

Multiple sources of data will be collected, including electronic medical records (EMRs); mobile phone or web entry in the Fostering Connections web application; and self-reports from the FCFNs, youth, and caregivers (Textbox 1). Cascade mental health services–level data will be extracted from EMRs at baseline and at 1, 3, and 6 months for participants in both conditions. Assessments will be conducted via mobile phone or tablet device, depending on participant preference.

Study measures.

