##### Motivation for Youth’s Treatment Scale

This is a psychometrically valid 8-item scale that youth and caregivers complete to measure intrinsic treatment motivation with the subscales of problem recognition and treatment readiness [44].

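### The mediator screen relates month-1 and month-3 values to cascade outcomes without requiring the outcome to come later, so a variable that treatment changed could be carried forward as a candidate mediator

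*Protocol article*

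**What the plan says.** The Cascade Outcomes section describes the potential mediators as "measured longitudinally (at baseline and at 1, 3, and 6 months) only for FCFN intervention participants". It then sets out a two-step screen. The first step asks which variables change between baseline and month 1 or month 3. The second step is "examining whether month 1 or month 3 values and changes between baseline and month 1 or month 3 are associated with cascade outcomes". The section limits what this can show: "It will not be possible to test mediation without data from the control group". The stated aim is that "we will identify potential mediators to be studied in the future trial".

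On timing, the Intervention Condition section says: "Families (n=40) who are randomized to the FCFN intervention will complete six 60-minute intervention sessions in the first 2 to 3 months of the 6-month" study window. Under Assessment Data Collection, cascade "data will be extracted from EMRs at baseline and at 1, 3, and 6 months for participants in both conditions". Table 1 defines engagement as staying in treatment for at least six weeks. Primary Outcome Measures lists time to referral and time to initiation in days. Under Recruitment and Consent, families are introduced to the study when they see clinic staff, for example at the screening visit.

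The Hypotheses section names youth treatment motivation and perceived barriers among the mechanisms. The motivation scale is said to "measure intrinsic treatment motivation with the subscales of problem recognition and treatment readiness".

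**The concern.** A variable is a plausible mediator of an outcome only if it changed before the outcome occurred. The screen uses follow-up mediator values but does not restrict the outcomes to later ones. A youth who began therapy in week 4 and reports greater treatment readiness at month 3 counts in favour of motivation as a mediator, although the therapy may have produced the readiness.

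Neither step of the screen would expose this. If starting treatment raises motivation, motivation changes from baseline and so passes the first step. It also correlates with initiation and so passes the second. The analysis has no control-arm comparison to reveal the problem.

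What is at stake is the choice of mechanisms for the future trial, which is the stated purpose of this analysis.

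**Working it through.** **Which outcomes can come first.**
- *Screening*: can coincide with or precede baseline, since families may be recruited at the screening visit.
- *Referral and initiation*: can fall before month 1 or month 3. The navigator sessions are concentrated in the first 2 to 3 months, so starts before the month-3 questionnaire are to be expected if the intervention works.
- *Six-week engagement*: month 3 is about 13 weeks, and 13 − 6 = 7, so a youth who starts in the first 7 weeks can be engaged by then. Month 1 is shorter than six weeks, so engagement cannot be complete by month 1 if treatment starts after baseline.

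**Inputs for the size.** The plan states no error rate or power for this screen, so there is no figure to reproduce. From the article: 40 youth in the FCFN arm. Assumed, because the article does not give them:
- p3, the share started by month 3: 10–45%.
- p6, the share started by month 6: 40–70%.
- d, the rise in the month-3 mediator caused by having started: 0.3, 0.5 or 0.8 SD.
- The mediator has no effect on initiation.
- Two-sided 5% t-test of the month-3 value by initiation status at month 6.

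**Formula.** Only those started by month 3 are shifted, and they make up p3/p6 of all who start by month 6. The spurious difference between starters and non-starters is therefore d × p3/p6.
- p3 = 45%, p6 = 69%, d = 0.5: 0.5 × 0.45/0.69 = 0.33 SD. Group sizes are 40 × 0.69 = 27.6 and 12.4, so the standard error is √(1/27.6 + 1/12.4) = 0.34 SD.
- p3 = 45%, p6 = 55%, d = 0.8: 0.8 × 0.45/0.55 = 0.65 SD. Groups of 22 and 18 give a standard error of 0.32 SD.
- p3 = 10%, p6 = 40%, d = 0.3: 0.3 × 0.10/0.40 = 0.075 SD. Groups of 16 and 24 give a standard error of 0.32 SD.

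**Simulated rate of a falsely significant month-3 association** (6,000 or 20,000 runs per cell; a 20,000-run repeat of all the timings agreed to within about 1 percentage point):

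| Started by month 3 / month 6 | d = 0.3 | d = 0.5 | d = 0.8 |
|---|---|---|---|
| 10% / 40% | 5% | 7% | 9% |
| 20% / 40% | 8% | 12% | 22% |
| 20% / 45% | 7% | 11% | 19% |
| 28% / 45% | 9% | 15% | 32% |
| 28% / 69% | 6% | 8% | 13% |
| 45% / 69% | 8% | 14% | 28% |
| 45% / 55% | 12% | 24% | 49% |

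With d = 0 the rate is about 5%. Restricting to youth not yet started at month 3 and counting only later starts removes the shift, and the rate is about 5% in every scenario.

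**Month 1.** With 5–15% started by month 1 and 60–70% by month 6 (assumed), the rate is about 5% to 7% in nearly all combinations. The worst is 15% and 60% with d = 0.8: the shift is 0.8 × 0.15/0.60 = 0.20 SD with groups of 24 and 16. This is the same shift and split as the 10%/40% row at 0.8 SD, so the rate is about 9%.

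**What the landmark leaves.** At 45% and 69%, 40 × (1 − 0.45) = 22 youth remain at risk at month 3, with 40 × (0.69 − 0.45) = 9.6, about 10, later starts.

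**The case against.** - *The plan draws no causal conclusion.* This stands. A reader might infer that treatment-driven motivation would be reported as motivation driving treatment. The article does not support that: it says mediation cannot be tested, speaks of association, and only nominates candidates. The harm is limited to a poor nomination.
- *The plan is already partly ordered.* This stands in part. Month-1 and month-3 values are related to outcomes and month-6 values are not, which suggests order was intended. It works fairly well at month 1 but is not secured at month 3.
- *The size rests on unknown timing.* This stands. It is tempting to read initiation timing from the Background figures ("with only 28% of all youth assessed within 2 months of case opening, 45% by 3 months, and 69% by 6 months"). Those are full assessments counted from case opening, so neither the event nor the clock matches. The 45%/69% row shares their values but is only one assumed scenario.
- *The simulation covers only the second step.* This stands. The rates are for the association, not for passing the whole screen, and the article sets no significance level for it.
- *A condensed article may leave a lag rule to the full plan.* This carries some weight, and nothing in the article prevents adding such a rule. But the article does state its selection rule, and that rule, followed as written, admits outcomes that came first.

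**Conclusion.** The point holds for the exploratory mediator screen, mainly at month 3. As written, the rule lets an outcome that preceded the mediator measurement count as evidence for that mediator. Under the assumed timings and reverse effects, false significance at month 3 ranges from close to nominal (about 5%) to 49%. A false flag is therefore possible but far from certain, and the figure depends heavily on when youth start treatment. At month 1 the inflation is small.

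A reader might also infer that the trial's main result is at risk. It is not: the randomized comparison of initiation and engagement does not use these mediator values. The point is moderate in weight and worth correcting before analysis because the remedy needs no new data.

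**What to change.** For each cascade step, relate the mediator value, or its change from baseline, only to events dated after that assessment, among youth who had not reached the step by then. Make month 1 the main landmark and month 3 secondary, using the event dates in the medical record. Alternatively, enter the mediator as a time-varying covariate in the Cox regression already planned for time-to-event outcomes.

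Steps completed before the assessment should not be used to nominate mediators. Substituting the baseline value for those steps does not help: a value recorded before the intervention began cannot show a change that the intervention produced.

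The cost is a few sentences of analysis text and a loss of information. At the month-3 landmark about 22 of 40 youth and 10 later events would remain under the 45%/69% assumption, and only 40 × (0.55 − 0.45) = 4 later events under 45%/55%. Month-3 results should therefore be presented as descriptive, with the numbers at risk and of later events shown.
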